**N/A**

6.7 For Humanitarian Use Device (HUD) uses provide a description of the device, a summary of how you propose to use the device, including a description of any screening procedures, the HUD procedure, and any patient follow-up visits, tests or procedures.

**N/A**

# Data and Specimen Banking*

7.1 If data or specimens will be banked for future use, describe where the specimens will be stored, how long they will be stored, how the specimens will be accessed, and who will have access to the specimens.

We will store identifiable information (including PHI) for future research purposes.

Data from this study, including PHI related to research, will be stored for 6 years after conclusion of the study.  Data will be stored in a secured folder on the NCH network and REDCap servers, accessible to members of the study team. Study staff will access the information after logging into the NCH secure network.

7.2 List the data to be stored or associated with each specimen.

**N/A** – no specimens to be stored

7.3 Describe the procedures to release data or specimens, including: the process to request a release, approvals required for release, who can obtain data or specimens, and the data to be provided with specimens.

**N/A** – no specimens to be stored

# Sharing of Results with Subjects*

8.1 Describe whether results (study results or individual subject results, such as results of investigational diagnostic tests, genetic tests, or incidental findings) will be shared with subjects or others (e.g., the subject’s primary care physicians) and if so, describe how the results will be shared.

Speech, language, and literacy outcome measures that are collected as part of routine clinical care will be reported to the family, as part of standard care by the therapists. Typical clinical documentation and correspondence with referring and treating providers will be maintained.

# Study Timelines*

- 1. Describe: The duration of an individual subject’s participation in the study.

Each child is anticipated to participate in 2 separate 6-month intervention periods (Intervention Period #1/SLT-only and Intervention Period #2/SLT+Digital), for a total of 12 months. See **Figure 2**. SLP visits may be either evaluations or therapy sessions and are part of standard care. Evaluations at the start of therapy and in 6 month intervals may take 2-2.5 hours each (such as the **Pre-Trial SLP Evaluation, Post-SLT SLP Evaluation, and Post-SLT + Digital SLP Evaluation)**. In-person therapy frequency is determined by SLP_T_ and may range from monthly to weekly. Duration of therapy sessions are typically 1 hour. All of the sessions in this study will be done as part of standard of care visits. There are no additional research visits, unless necessary to collect survey data or requested by the participating caregiver.

- 1. Describe: The duration anticipated to enroll all study subjects.

Feasibility analysis of local subjects (Section 12) indicates 411 D/HH children were seen in 2019 in the age group we are examining. Of these, 141 children had a speech and language evaluation billed in that year. Our power analysis motivates us to recruit a total of 50 patients. It we account for eligibility, choice of participation, and patient volume, we anticipate approximately **9 months-1 year** to recruit fully.

- 1. Describe: The estimated date for the investigators to complete this study (complete primary analyses)

With rolling recruitment and intervention, expected recruitment, and 1 year treatment period, we anticipate approximately **2-2.5 years from start of study** to completion of primary analysis.

# Inclusion and Exclusion Criteria*

Children seen in the Hearing Program at Nationwide Children’s Hospital who are deaf/hard of hearing are eligible. This includes Main Campus and off-site locations, in the departments that make up the multidisciplinary Hearing Program (Pediatric Otolaryngology, Audiology and Speech-Language Therapy). Additionally, their parent/caregiver and treating SLP will be invited to participate.

**Child Eligibility:**

- ***Inclusion:***
  - Children ages 3.0-5.11 years at time of initial assessment and
    - Auditory neuropathy in both ears, or
    - Bilateral Sensorineural or mixed hearing loss at least (PTA≥30dB)
- ***Exclusion:***
  - English not primary language (app is English only at present)
  - standard score CLS >2 SD from normal on CELF-P3

**Parent/Caregiver Eligibility:**

- ***Inclusion:***
  - Parent/caregiver of eligible child (must be child’s legal guardian)
- ***Exclusion:***
  - None

**Treating SLP Eligibility:**

- ***Inclusion:***
  - Treating therapist/SLP for participating child
- ***Exclusion:***
  - None

# Vulnerable Populations*

11.1 If the research involves individuals who are vulnerable to coercion or undue influence, describe additional safeguards included to protect their rights and welfare.

This research study does NOT involve pregnant women, neonates, prisoners, or cognitively impaired adults.

This research involves no greater than minimal risk for children or adults.

PHI will only be shared with the groups listed below:

- PI and Study Staff
- The Nationwide Children’s Hospital Institutional Review Board (the committee that reviews all human subject research)
- Nationwide Children’s Hospital internal auditors
- Participant’s insurance company

PHI will be protected in the following ways:

- Research records will be stored in a locked cabinet in a secure location
- Research records will be stored in a password-protected computer file
- The list linking the assigned code number to the individual subject will be maintained separately from the other research data
- Only certified research personnel will be given access to identifiable participant information

# Local Number of Subjects

12.1 Indicate the total number of subjects to be accrued locally.

A **power analysis** was performed, based off of Raw Scores with the following rationale: A repeated measures design will evaluate the effect of the intervention within person. In this case, the primary goal of the study is to compare the change across time during SLT therapy alone to the change across time with SLT + Digital. A sample size of 43 achieves 90% power to detect a mean of paired differences of 0.75 with an estimated standard deviation of 1.0 and with a significance level of 0.001 using a two-sided paired t-test.   We plan to enroll 50 children at NCH, as well as a parent/caregiver for each child and the child’s treating SLP.

12.2 If applicable, distinguish between the number of subjects who are expected to be enrolled and screened, and the number of subjects needed to complete the research procedures (i.e., numbers of subjects excluding screen failures.)

We expect approximately 411 unique D/HH children in the age range to be seen by our Hearing Program in 1 year, based on 2019 data. Of these, 141 completed a speech and language evaluation in that year and 270 did not. With prospective attention to scheduling and these volumes, we anticipate screening approximately 250-300 patients to achieve 50 that would enroll.

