# Data Management* and Confidentiality

17.1 Describe the data analysis plan, including any statistical procedures or power analysis.

Raw Score, Standard Score, Percentile Rank, Age Equivalent, and Growth Scale Values for the assessment tests will be measured. Power analysis was based off of Raw Score. A 2-by-2 repeated measures design consists of two groups of subjects, each measured at two time points. In this case, the primary goal of the study is to compare the change across time in group 1 to the change across time in group 2. Sample sizes of 13 in group 1 and 13 in group 2 achieve 92% power to detect a difference in mean changes of 2.0 with a standard deviation of 1.0 at the first time point, a standard deviation of 1.0 at the second time point, and a correlation between measurement pairs of 0.300. The significance level (alpha) is 0.010 using a two-sided, two-sample t-test. To detect a mean 1.5 point difference (all else being equal), we would need **21 patients in each group**. To detect a mean 1 point difference (all else being equal), we calculate we would need 44 patients in each arm.

We plan to analyze Intervention Period 1 (SLT) and Intervention Period 2 (SLT+Digital) together using mixed-effects models to account for differences between interventions 1 and 2. For the primary outcomes, evaluate baseline assessments and compare values between groups using Pearson chi-square tests, t-tests, and Wilcoxon-Mann-Whitney tests. If any imbalance in patient characteristics (e.g. age, frequency of therapy) is detected between groups, the imbalanced characteristics will be adjusted for in multivariable mixed-effects linear regression analyses.

All statistical analyses will be conducted using SAS Enterprise Guide, version 7.15 (SAS Institute Inc). Outcomes are reported for the intention-to-treat population and the also reported for the per protocol population. A 2-sided P < .05 was considered statistically significant.

17.2 Describe the steps that will be taken to secure the data (e.g., training, authorization of access, password protection, encryption, physical controls, certificates of confidentiality, and separation of identifiers and data) during storage, use, and transmission.

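### Sections 12.1 and 17.1 give incompatible power calculations: the SD of 1.0 behind 43 children and 90% power cannot hold with 17.1's SD and correlation, and 17.1's group sizes belong to a two-group design.

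*Protocol*

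**What the plan says.** Protocol Section 12.1 (Local Number of Subjects) states the target of the trial: "the primary goal of the study is to compare the change across time during SLT therapy alone to the change across time with SLT + Digital". Its calculation "was performed, based off of Raw Scores with the following rationale" and reads "A sample size of 43 achieves 90% power to detect a mean of paired differences of 0.75 with an estimated standard deviation of 1.0", "with a significance level of 0.001 using a two-sided paired t-test". The enrolment target follows: "We plan to enroll 50 children at NCH". Section 9 (Study Timelines) says that the power analysis is the reason for recruiting 50.

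Section 17.1 (Data Management and Confidentiality) contains a second calculation, also on Raw Score. It describes two groups of subjects, each measured twice and compared by a two-sample t-test at alpha 0.010. It assumes SD 1.0 at the first time point, "a standard deviation of 1.0 at the second time point, and a correlation between measurement pairs of 0.300". It gives 13 per group for a difference of 2.0 (92% power), 21 per group for 1.5, and then: "To detect a mean 1 point difference (all else being equal), we calculate we would need 44 patients in each arm". The same section sets two-sided P < .05 as the significance level for the analysis.

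Section 6 (Procedures Involved) describes one cohort: every child has 6 months of SLT-only and then 6 months of SLT+Digital. Section 4 (Study Endpoints) places the assessments pre-trial, at 6 months and at 12 months.

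**The concern.** With three assessments per child, the comparison in 12.1 is the second change minus the first. Writing Y0, Y6 and Y12 for the scores, this is (Y12 - Y6) - (Y6 - Y0) = Y12 - 2·Y6 + Y0. The 6-month score counts twice, so this contrast is more variable than a single score unless the visits are strongly correlated. Section 12.1 gives it an SD of 1.0. Section 17.1 gives each single score an SD of 1.0 and a correlation of only 0.300. Both are current text on the same scale, and neither says that it replaces the other.

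The enrolment target rests on the 12.1 figure. If 17.1's inputs are nearer the truth, a null result could be read as a negative finding from a 90%-powered trial when it is not. The reader is also left with two sample-size justifications for different designs, and with no clear alpha.

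**Working it through.** **Inputs.** From 12.1: n = 43, difference 0.75, SD 1.0, alpha 0.001, two-sided paired t-test. From 17.1: SD 1.0 per visit, correlation 0.300, alpha 0.010 for power and 0.05 for analysis. The 0-to-12-month correlation, r02, is not in the protocol, so a range is shown. Power is from the noncentral t distribution.

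**1. Reproduce 12.1.** Noncentrality = (0.75/1.0)·√43 = 4.92 on 42 df. At two-sided alpha 0.001 the power is 90.4%, and 43 is the smallest n that reaches 90%. With 50 children it is 95.7%. The arithmetic is right given its inputs.

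**2. Reproduce 17.1.** SD of one change = √(1 + 1 - 2·0.3) = √1.4 = 1.183. A two-sample t-test at alpha 0.010 gives 92.4% (13 per group, difference 2.0), 91.3% (21 per group, 1.5) and 90.5% (44 per group, 1.0). These figures are right for two independent groups.

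**3. SD of the 12.1 contrast under 17.1's inputs.** With unit SDs,

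Var(Y12 - 2·Y6 + Y0) = 6 - 4·r01 - 4·r12 + 2·r02.

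With r01 = r12 = 0.30 this is 3.6 + 2·r02. A valid correlation matrix requires r02 ≥ 2·0.09 - 1 = -0.82, so the variance is at least 3.6 - 1.64 = 1.96 and the SD at least 1.40.

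Power for 0.75 points:

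| r02 | SD | n=43, alpha 0.001 | n=50, alpha 0.001 | n=43, alpha 0.05 | n=50, alpha 0.05 |
|---|---|---|---|---|---|
| 0.30 (equal correlations) | 2.05 | 15% | 20% | 65% | 72% |
| 0.09 (first-order autoregressive) | 1.94 | 18% | 24% | 70% | 76% |
| 0 | 1.90 | 19% | 26% | 72% | 78% |
| -0.82 (mathematical floor) | 1.40 | 50% | 61% | 93% | 96% |

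No admissible r02 gives an SD of 1.0. Even the SD of a single 6-month change is 1.18.

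**4. Dependence on the correlation.** If all three correlations equal rho, SD = √(6(1 - rho)). Power for 0.75 points:

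| rho | SD | n=43, alpha 0.001 | n=50, alpha 0.001 | n=43, alpha 0.05 | n=50, alpha 0.05 |
|---|---|---|---|---|---|
| 0.5 | 1.73 | 26% | 35% | 79% | 85% |
| 0.7 | 1.34 | 56% | 67% | 95% | 97% |
| 0.83 | 1.00 | 90% | 96% | over 99% | over 99% |

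**5. Detectable difference.** With SD 2.05 and 43 completers, 90% power needs 1.53 points at alpha 0.001 or 1.04 at 0.05.

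**6. Why 17.1's sizes do not transfer.** Its test treats the two changes as independent. Here they come from the same child and share Y6. Their covariance is r01 + r12 - r02 - 1, so with 17.1's 0.300 their correlation is -0.70/1.4 = -0.5 if r02 = 0.30, -0.49/1.4 = -0.35 if r02 = 0.09, and -0.40/1.4 = -0.29 if r02 = 0. A negative correlation makes the difference between the changes more variable than independence would.

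**The case against.** The strongest reply is that 12.1 is the operative calculation and 17.1 an unreconciled two-group text. 12.1 is within-person, needs 43 and enrols 50, whereas 44 per arm would mean 88 children. If 17.1 is dropped, its correlation of 0.300 goes too, and the 12.1 SD is then unsupported rather than shown to be wrong. The text attaches that SD to the paired differences and calls it estimated, so it could come directly from data. This stands as a limit on the point: a common correlation of about 0.83 would make 12.1 exact.

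Two stronger readings are tempting. A reader might infer that the authors put the single-visit SD in place of the SD of the contrast. The equal values suggest it, but the protocol does not say where the 1.0 came from. A reader might also infer that the design is simply underpowered, at about 15%. That figure combines the strictest alpha, 17.1's low correlation and 43 rather than 50 children. At the declared 0.05 with 50 children, power is 85% at a common correlation of 0.5. The documents do not establish the true correlation, so they do not support an unconditional claim.

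Section 2 (Background and Objectives) also calls the study a pilot to inform larger ones, which softens the harm of a misread null result. It does not remove the contradiction, because 12.1 still claims 90% power for a stated comparison. Nor does reading 0.75 as a standardised effect: 12.1 says Raw Scores, and 0.75 SDs of this contrast would be 0.75·2.05 = 1.5 raw points under 17.1's values with equal correlations.

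**Conclusion.** The contradiction holds. With 17.1's 0.300 applied to both 6-month intervals, the SD of the 12.1 contrast is at least 1.40 for any admissible 0-to-12-month correlation, so 12.1's 1.0 and 17.1's inputs cannot both be right. How much power is lost is conditional. It falls from the stated 90% to 15-19% with 43 children at alpha 0.001 if 17.1's values are right and r02 lies between 0 and 0.30, and much less is lost if the visits are more strongly correlated or if 0.05 is the operative alpha.

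Two further faults do not depend on any assumption. The 13, 21 and 44 per group answer a question for two independent groups, which this trial does not have. And three significance levels (0.001, 0.010 and 0.05) stand side by side without a statement of which one governs, although the choice moves power under 17.1's inputs from below 20% to 65% or more with 43 children.

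**What to change.** - Delete the two-group calculation from Section 17.1.
- Keep one calculation in 12.1, for Y12 - 2·Y6 + Y0 on a named primary score, at one alpha that matches the analysis.
- Take the SD of that contrast from a direct estimate with its source, for example the clinic's existing 6-monthly ROWPVT-4 and CELF-P3 records. Failing that, derive it from sigma and all three pairwise correlations. Use sigma·√(6(1 - rho)) only if equal SDs and equal correlations are stated as an assumption.
- Keep N=50 and restate the power or the detectable difference over a range of correlations. With 17.1's values and equal correlations, 43 completers detect about 1.0 raw point at alpha 0.05, or 1.5 at 0.001, with 90% power.
- If a direct estimate of 1.0 already exists, cite it in 12.1; the 0.75 can then stay.

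The cost is protocol wording and possibly a short look at existing records. No extra children are needed and conduct does not change. The downside is that the stated figure will probably be less favourable.

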# Recruitment Methods

- 1. Describe when, where, and how potential participants will be recruited.

Participation is completely voluntary; refusal to participate will involve no penalty or loss of benefits to these potential subjects. No attempts at coercion will be made.

**Child and Parent/Caregiver Participants:**

Upon approval by the NCH IRB, recruitment efforts will begin. Potential patients will be identified by study staff, audiologists, SLPs, nurses, and physicians in the ENT department at NCH, along with data requests obtained from the EDW at NCH. Study eligibility and exclusionary criteria will be made known to those involved in identifying eligible participants individuals in advance.

Written documentation of informed consent will be obtained and documented from parents/caregivers or legal guardians of each prospective participant who meet inclusion and exclusion criteria who agree to participate.

This study will implement a multi-pronged (3 strategies described below) recruitment approach for child and parent/caregiver participants.

Eligibility will be assessed in EPIC based on child’s date of birth, diagnosis, primary language, treatment, treatment dates, treatment location, providing clinicians, and speech therapy assessment scores. After identification via EPIC and/or EDW, clinicians will be notified about potentially eligible participants on their schedule. During the appointment, clinicians will inquire if the family agrees to be contacted by the study coordinator for more information about the Hear Me Read study. If family agrees, study staff will be notified and will meet with/contact the family to review the study information and recruit the family using the **Recruitment Script** as a guide. This may be done while the family is on-site or via phone or email after their visit. If research staff is unable to meet family at the clinic to review study information and recruit after family verbally agrees to be contacted, research staff will contact family via phone call and/or email. If the family wishes to participate, eligibility is assessed and enrollment proceeds if confirmed.

In addition to identifying eligible children in advance of their clinical appointment, recruitment will also be done by posted and digital flyers. A paper recruitment flyer (**Hear Me Read 2021 Recruitment Flyer)** will be placed in public areas of targeted NCH facilities (such as clinical therapies, ENT, Audiology) at Main and Close To Home locations so that families may know about and volunteer to participate. Digital version of **Hear Me Read 2021 Recruitment Flyer** will be sent through NCH distribution channels through the Research Institute and Marketing. No incentive is provided to post. Study coordinator information will be on the flyers and interested families will be instructed to contact the study coordinator.

The **Hear Me Read 2021 Recruitment Email/Letter** will be sent to established patients in the NCH Hearing Program. Emails may be sent via myChart, in line with hospital policies for this recruitment method or via direct email or mail contact. Study coordinator information will be included in the email/letter and interested families will be instructed to contact the study coordinator. Study staff will contact (e.g., call, text, email) caregiver approximately one to two weeks after the initial email or letter has been sent if study staff does not receive a response. The email/letter offers an option to opt-out if caregiver wishes to receive no further information about the study.

***Treating SLP Participants:***

BTO study staff will reach out to Speech Language Pathologists who treat eligible children. This includes SLPs in the departments that make up the multidisciplinary Hearing Program (Pediatric Otolaryngology, Audiology and Speech-Language Therapy) and those external to NCH. Study staff will contact SLPs via phone and/or email to provide information about the HMR study.

Consent will be obtained consistent with the Waiver of Written Documentation regulations as outlined in Section 22 of this protocol. Participating Speech Language Pathologists will receive a SLP packet for each enrolled child participant.

13.2 Describe the source of subjects.

The children in this study will consist of D/HH patients in the Hearing Program at NCH, seen through the ENT, audiology, and Speech-language Therapy departments. Their parent/caregiver, as well as their treating SLP will also be invited to participate.

13.3 Describe the methods that will be used to identify potential subjects.

See above, section 13.1

13.4 Describe materials that will be used to recruit subjects. (Attach copies of these documents with the application. For advertisements, attach the final copy of printed advertisements. When advertisements are taped for broadcast, attach the final audio/video tape. You may submit the wording of the advertisement prior to taping to preclude re-taping because of inappropriate wording, provided the IRB reviews the final audio/video tape.)

- **Hear Me Read 2021 Recruitment Flyer**
- **Hear Me Read 2021 Recruitment Email/Letter**

13.5 Describe the amount and timing of any payments to subjects.

Incentive ($10/survey) will be offered to children’s’ parents/caregivers and treating speech-language pathologists, and provided upon completion of surveys. We will use GreenPhire Clincards through NCH as incentives for completion of surveys as follows:

- - Treating Therapists:
    - Post-intervention #1 (SLT) - Treating Therapist at 6 months
    - Post-intervention #2 (SLT+Digital) – Treating Therapist at 12 months
  - Parents/Caregivers
    - Pre-trial parent/caregiver survey – Parent/Caregiver at enrollment
    - Post-intervention #1(SLT) - Parent/Caregiver at 6 months
    - Post-intervention #2 (SLT+Digital) – Parent/Caregiver at 12 months

Participants can choose to not provide this, without penalty. Surveys will be electronic, done via REDCap.

